### **13.5 Reporting urgent safety measures**

MFT SOP Pharmacovigilance for Trust-Sponsored Clinical Trials of Investigational Medicinal Products (CTIMPs) must be followed.

If any urgent safety measures are taken the CI/Sponsor shall immediately and in any event no later than 3 days from the date the measures are taken, give written notice to the MHRA and the relevant REC of the measures taken and the circumstances giving rise to those measures.

### 13.6 Notification of deaths

Deaths and all Serious Adverse Events (SAEs) that are assessed to be caused by the IMP will be reported to the sponsor. This report will be immediate.

### 13.7 Pregnancy reporting

MFT SOP Pharmacovigilance for Trust-Sponsored Clinical Trials of Investigational Medicinal Products (CTIMPs) must be followed.

- All pregnancies within the trial (either the trial participant or the participant's partner) should be reported to the Chief Investigator and the Sponsor using the relevant Pregnancy Reporting Form within **within 24 hours of learning of the event**.
- Pregnancy is not considered an AE unless a negative or consequential outcome is recorded for the mother or child/foetus. If the outcome meets the serious criteria, this would be considered an SAE.

Follow-up of pregnant subject: Any pregnancy will be monitored as deemed appropriate depending on the informed consent given.

Follow-up of child born to a pregnant trial subject, or to the partner of a male trial subject: Any pregnancy will be monitored as deemed appropriate depending on the informed consent given.

### 13.8 Overdose

- Overdoses should be notified to sponsor .
- Overdoses will be identified from pill counts, diary cards, drug charts and patient comment.
- The affect of an overdose on the final analysis will determined on a case by case basis.
- If an SAE is associated with the overdose ensure the overdose is fully described in the SAE report form.

### 13.9 Treatment Stopping Rules

The trial may be prematurely discontinued by the Sponsor, Chief Investigator or Regulatory Authority on the basis of new safety information or for other reasons given by the regulatory authority or ethics committee concerned.

If the trial is prematurely discontinued, active participants will be informed and no further participant data will be collected. The Competent Authority and Research Ethics Committee will be informed within 15 days of the early termination of the trial.

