#### 4. Trial Summary

A summary of trial procedures is provided in Appendix 4.

30 premenopausal women at moderate to high risk of BC (NICE guidelines) will be recruited from family history clinics in a similar manner to previous successful biopsy and dietary intervention studies (Ong 2009; Evans 2010), using mailshot and clinic visit recruitment. Subjects will be confirmed to be in an ovulatory menstrual cycle prior to performance of baseline breast MRI scan and vacuum assisted biopsy (VAB) of the most dense region of one breast. Ideally 10 cores of breast tissue will be taken. After the onset of the next menstrual cycle subjects will start UA 5mg daily and be reviewed every 4 weeks in trial clinics for blood tests and toxicity assessment. In the 12th week of therapy subjects will have a repeat breast MRI scan followed by either VAB of the contralateral breast or prophylactic mastectomy with harvest of breast tissue (from the predetermined contralateral isodense region from baseline MRI). UA will then be discontinued and one further safety visit planned for 4 weeks post completion (figure 2).

Once the participant has had their visit 4 appointment they will be sent an invite to provide a saliva sample for the purpose of DNA analysis. Should they wish to participate in this part of the study a telephone appointment will be made for them. At this appointment a study doctor will discuss the analysis which will be undertaken. Following the discussion, if the participant is happy to proceed, they will be sent a consent form to complete and return to research team.

Once the consent form has been received by the study team, a helix tube for saliva collection will be posted to the participant. The participant will be provided with a return envelope to post the sample to the genetics team at St Mary's Hospital, Manchester.

When the results of the DNA analysis are available an appointment will be made for the participant to be reviewed either as a telephone appointment or to attend the Nightingale Centre for feedback with a study doctor.

Figure 2: Trial schema

[figure not shown]

The end of the trial will be when the last participant has received their DNA analysis results – no further data will be collected after this point.

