### 6.3 Withdrawal of Subjects

Participants have the right to withdraw from the study at any time for any reason. The investigator also has the right to withdraw patients from the study drug in the event of inter-current illness, AEs, SAE's, SUSAR's, protocol violations, administrative reasons or other reasons. It is understood by all concerned that an excessive rate of withdrawals can render the study un-interpretable; therefore, unnecessary withdrawal of patients should be avoided. Should a patient decide to withdraw from the study, all efforts will be made to report the reason for withdrawal as thoroughly as possible. Should a patient withdraw from study drug only, efforts will be made to continue to obtain follow-up data, with the permission of the patient.

The reason for withdrawal will be recorded in the CRF.

If the participant is withdrawn due to an adverse event, the investigator will arrange for follow-up visits or telephone calls until the adverse event has resolved or stabilised.

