**Visit 4 Day 113  $\pm$  4 days (week 17)**

During this visit the participant will:

- be asked if they are happy to continue in the trial
- have adverse events from the VAB visit and any other adverse events documented
- have any changes in their concomitant medications documented
- have their weight recorded
- have blood samples taken for LFT of which bilirubin, ALT, ALP, LDH will be measured
- be asked if they have started their menstrual period

Should a participant experience treatment emergent clinical symptoms or signs of liver disease whilst participating in the study they will be advised to contact the research team as soon as possible for assessment which will include repeat LFTs of which bilirubin, ALT, ALP and LDH will be recorded. Therefore, assessments of this nature could be conducted outside of the scheduled study visits.

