### 13.1 Recording and reporting of SAEs AND SUSARs

**MFT SOP Pharmacovigilance for Trust-Sponsored Clinical Trials of Investigational Medicinal Products (CTIMPs) must be used for safety reporting.**

AEs, ARs, SAEs, SARs and SUSARs must be recorded and reported as follows:

- For AEs / SAEs – from consent until the time of the last participant visit
- For ARs / SARs and SUSARs – from the 1st IMP dose until the time of the last participant visit

All AEs must be recorded in the participant's CRF in the AE log and in the patient's family history notes. SAEs/SARs/SUSARs must be recorded in the participant's CRF in the AE log and in the patient's family history medical records and must be reported to the Sponsor and other relevant departments/individuals **within 24 hours** of the research staff becoming aware of the event according to the instructions in **SOP Pharmacovigilance for Trust-Sponsored Clinical Trials of Investigational Medicinal Products (CTIMPs) must be used for safety reporting.**

(S)AEs and (S)ARs will be evaluated for duration and intensity according to National Cancer Institute Common Terminology Criteria for Adverse Events V4.0 (NCI-CTCAE) or MedDRA (Medical Dictionary for Regulatory Activities)

Investigator reports of suspected SARs will also be reported by the CI or their delegate to Gedeon Richter (manufacturer).

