### **13.4 The type and duration of the follow-up of subjects after adverse events.**

Adverse events will be followed up until the safety visit 4 weeks after the last dose of IMP.

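### Section 13.9 ends all participant data collection on early termination, even a stop for safety, with no exception for the off-drug safety visit or open adverse events

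*Protocol*

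**What the plan says.** Section 13.9 lets the sponsor, chief investigator or regulator end the trial early "on the basis of new safety information or for other reasons given by the regulatory authority or ethics committee concerned". The next paragraph sets what happens then: "If the trial is prematurely discontinued, active participants will be informed and no further participant data will be collected". No exception follows.

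Other current sections set safety follow-up duties without mentioning early termination:

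- **Section 13.4:** "Adverse events will be followed up until the safety visit 4 weeks after the last dose of IMP".
- **Section 4:** "UA will then be discontinued and one further safety visit planned for 4 weeks post completion".
- **Section 7.1, Visit 4 (Day 113 ± 4 days):** adverse events are reviewed and women "have blood samples taken for LFT of which bilirubin, ALT, ALP, LDH will be measured".
- **Section 6.3, withdrawal because of an adverse event:** "the investigator will arrange for follow-up visits or telephone calls until the adverse event has resolved or stabilised".
- **Section 6.3, leaving the drug only:** "Should a patient withdraw from study drug only, efforts will be made to continue to obtain follow-up data, with the permission of the patient".
- **Section 13.1:** adverse events and serious adverse events are recorded "from consent until the time of the last participant visit".

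**The concern.** A stop prompted by new safety information is when off-drug liver results and the outcomes of open events are most needed. Section 13.9 says to stop recording at exactly that point.

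The protocol itself treats the liver as a monitored risk. Section 5.6.4 requires permanent discontinuation when ALT exceeds three times the upper limit of normal, and liver tests are scheduled at Visits 1 to 4. The side-effect profile is a secondary endpoint (section 8.4.2). Section 16 convenes no independent data monitoring committee and leaves safety review to the trial management group, which can work only from what has been recorded.

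At stake is the safety record of women on ulipristal acetate (UA), or within about 4 weeks of their last dose, when the trial stops. The primary endpoint is not at stake.

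**Working it through.** **1. The rules side by side**

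| Situation | Follow-up stated | Section |
|---|---|---|
| Completes treatment | Safety visit 4 weeks later, with adverse-event review and liver tests | 4, 7.1, 13.4 |
| Withdrawn because of an adverse event | Until the event has resolved or stabilised | 6.3 |
| Leaves the drug only | Follow-up data sought, with her permission | 6.3 |
| Whole trial stopped, including for safety | No further participant data | 13.9 |

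Nothing says which rule prevails. If 13.4 governs, 13.9 is wrong as worded. If 13.9 governs because it is the specific rule, off-drug safety recording ends for every woman active at the stop, and one woman withdrawn for an adverse event is followed for longer than a group stopped for a safety signal. Both readings call for the same correction.

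Section 13.1 does not fill the gap. It records events only up to the last participant visit, and if 13.9 is followed no later visit yields data. The unscheduled liver tests in section 7.1 apply only while a woman is participating in the study.

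**2. How long each woman is in the affected window**

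The end-of-treatment assessments fall on Days 78 to 85, and the safety visit is 4 weeks after the last dose. Counting from Day 1, the window W runs from 78 + 28 = 106 days to 85 + 28 = 113 days.

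**3. How many women a stop would catch**

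The protocol plans 30 women and gives no accrual period. Assume even entry over A days, with A = 365, 730 or 1,095.

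- Full occupancy: 30W/A.
- Average over stop dates from first entry to the last woman's safety visit: 30W/(A + W).
- Stop 30 days after first entry: 30 × 30/A.

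| Assumed accrual | Full occupancy | Average over the trial | Stop at day 30 |
|---|---|---|---|
| 12 months | 3180/365 = 8.7 to 3390/365 = 9.3 | 3180/471 = 6.8 to 3390/478 = 7.1 | 2.5 |
| 24 months | 3180/730 = 4.4 to 3390/730 = 4.6 | 3180/836 = 3.8 to 3390/843 = 4.0 | 1.2 |
| 36 months | 3180/1095 = 2.9 to 3390/1095 = 3.1 | 3180/1201 = 2.6 to 3390/1208 = 2.8 | 0.8 |

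Across the three scenarios the average is 8.8% to 23.6% of the 30 women.

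**4. What each woman caught would lose**

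She loses the record of her one scheduled off-drug liver test. At its nominal Day 29, Visit 1 comes 28 days into the window, which is 28/113 = 24.8% to 28/106 = 26.4% of it. A woman stopped in that interval would have no liver test on record after baseline.

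**The case against.** The strongest reply is that 13.9 can be read more narrowly. Section 13.4 is unqualified and nothing in 13.9 disapplies it. Section 4 uses similar words for the normal end of the trial, so the sentence may mean only that the research dataset closes. Section 13 also requires the sponsor's pharmacovigilance SOP to be used for safety reporting, and that SOP may require follow-up after a stop. These points make the actual loss uncertain. They do not repair the sentence: the narrower reading needs words that 13.9 lacks, the SOP is not shown, and 13.9 does not refer to it. An investigator who followed 13.4 would be departing from the wording of 13.9, and section 19 does not allow planned deviations.

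Three smaller points stand:

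- Section 13.9 bars data, not visits. Liver tests could still be done as clinical care, and what is lost is the trial record.
- Visit 4 is allowed from Day 109 to Day 117, so using its own dates moves the window slightly. Full occupancy at 12 months becomes 30 × 109/365 = 9.0 to 30 × 117/365 = 9.6.
- Every head-count rests on an assumed accrual period. They show that the number is small, not what it would be.

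**Conclusion.** The concern holds. Section 13.9 states a rule that, if followed, leaves a worse safety record in the very circumstance it provides for, and it contradicts sections 13.4 and 6.3. That conclusion rests on the text alone.

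The size is modest: at full occupancy roughly 3 to 9 women, assuming 30 women enter evenly over 36 down to 12 months. The Ki67 analysis, the sample size and clinical care are untouched, and there is no loss unless the trial stops early. It should be fixed because the conflict is explicit, it concerns participant safety, and the correction is cheap.

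**What to change.** Amend section 13.9 to say that, on early termination:

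- UA and the collection of efficacy and research data stop.
- Each woman who has taken UA is still offered a safety visit 4 weeks after her last dose, with adverse-event review and liver function tests, recorded with her agreement. It should be timed from her last dose, because Day 113 does not fit someone stopped partway through treatment.
- Adverse events open at the stop are followed until resolved or stabilised, as in section 6.3.

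The cost is one or two sentences by amendment. If a stop occurs, it adds one visit of an already planned type for each woman in the window (at most about 3 to 9 under the accrual assumptions used here), plus calls or visits for any open events.

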### 13.10 Development safety update reports

MFT SOP Pharmacovigilance for Trust-Sponsored Clinical Trials of Investigational Medicinal Products (CTIMPs) must be followed.

The CI, along with sponsor representatives, will submit DSURs once a year throughout the clinical trial, or on request to the Competent Authority (MHRA in the UK), Ethics Committee and Sponsor.

### 13.11 Signal review and trend analysis

#### 13.11.1 Safety signal review

MFT SOP Pharmacovigilance for Trust-Sponsored Clinical Trials of Investigational Medicinal Products (CTIMPs) must be followed.

#### 13.11.2 Trend analysis of adverse events

MFT SOP Pharmacovigilance for Trust-Sponsored Clinical Trials of Investigational Medicinal Products (CTIMPs) must be followed.

## 14 Finance

The trial is funded by a grant from **Breast Cancer Now**:  
[name],  
[name]  
Switchboard [name]  
[www.breastcancernow.org](http://www.breastcancernow.org)

## 15 Publication and dissemination

We will aim to publish this pilot study in a peer reviewed cancer prevention journal and present the data at national and international cancer/prevention conferences. This will be carried out following MFT's Publication, Dissemination and Clinical Impact of Research Results SOP. We will inform all study participants that they can request the results of the study.

## **16 Trial Governance**

A formal independent data monitoring committee will not be convened as this trial evaluates the repurposing of an agent shown to be safe in this age group of women in randomised controlled phase III studies. However, there remains a need to examine the safety and procedural data from the trial at regular intervals. The trial management group will take on this role.

### **16.1 Trial Management Group**

The Trial Management Group will be under the chairmanship of the Chief Investigator [name]. The TMG will meet formally at least every six months to review safety, recruitment and procedural data. A formal report will be produced every six months and a meeting of the TMG convened to discuss the findings. The minutes and conclusions of these meetings will be submitted to the Sponsor for review and to obtain the approval to continue with study procedures. The TMG will consist of the following clinical and laboratory investigators:

1. Chair - [name]
2. Recruiting clinicians: [name] and [name]
3. Consultant Radiologists: [name] and [name]
4. Imaging specialists: [name] and [name]
5. Basic scientists: [name], [name], [name], [name] (PDRA employed on the grant)
6. Research Nurses

To be quorate the TMG meeting needs to have at least 1 attendee from each of groups 1-6. The production of the 6 monthly reports in no way obviates the need for safety reporting detailed in section 9 and appendix 2.

## **17 Confidentiality**

All data will be kept strictly confidential according to Good Clinical Practice (GCP) Guidelines. All identifiable data will be stored by the Manchester University NHS Foundation Trust in a secure fashion in accordance with the MFT SOP 'Retention of Data, Off-Site Archiving and Destroying Documents'. Source data for the trial are the consent form, family and menstrual history, breast cancer risk assessment, blood test results, radiology results and

toxicity assessments. Data derived from analysis of patients' breast tissue will be held in the CRUK Manchester Institute and The Stopford Building at the University of Manchester associated with the participants trial number only. No patient identifiable data will be stored at either of these sites.

## 18 Quality Control

Monitoring of this trial will be to ensure compliance with Good Clinical Practice and scientific integrity will be managed and oversight retained, by the monitor assigned to monitor this trial as per the study monitoring plan. Data will be evaluated for compliance with the protocol and accuracy in relation to source documents. The monitors will verify that the clinical trial is conducted and data are generated, documented and reported in compliance with the protocol, GCP and the applicable regulatory requirements.

- an updated training record must be maintained for each member of the research team and retention of GCP training certificates which must be less than 3 years old
- protocol compliance will be monitored as part of the monitoring plan.

## 19 Protocol compliance

A "serious breach" is a breach which is likely to effect to a significant degree –

- (a) the safety or physical or mental integrity of the subjects of the trial; or
- (b) the scientific value of the trial

- prospective, planned deviations or waivers to the protocol are not allowed under the UK regulations on Clinical Trials and must not be used e.g. it is not acceptable to enrol a subject if they do not meet the eligibility criteria or restrictions specified in the trial protocol
- accidental protocol deviations can happen at any time. They must be adequately documented on the relevant forms and reported to the Chief Investigator and Sponsor immediately -. refer to procedure in SOP17 Recording and Reporting of Protocol Deviations and Violations, Serious Breaches of Protocol or GCP deviations from the protocol which are found to frequently recur are not acceptable, will require immediate action and could potentially be classified as a serious breach.
- the sponsor will be notified immediately of any case where the above definition applies during the trial conduct phase - refer to procedure in MFT's SOP 'Protocol and GCP Deviations, Violations and Serious Breaches in CTIMPs and Clinical Investigations of Medical Devices'

## 20 Amendments

The amendment history will be tracked using a log stored in the TMF.

**21 Insurance / Indemnity**

For the management of the research: Indemnity is provided through NHS schemes.

For the design of the research: Indemnity is provided through NHS schemes.

For the conduct of the research: Indemnity is provided through NHS schemes.

**Appendix 1: inhibitors/inducers of CYP3A4 not to be taken with UA**

**Potent inhibitors** of CYP3A4 that should not be taken with ulipristal acetate (summary of product characteristics 'not recommended')

ketoconazole, Itraconazole

ritonavir, Indanavir, Saquinavir, Nelfinavir

nefazodone

telithromycin, clarithromycin

Nefazodone

**Moderate inhibitors** of CYP3A4 that should not be taken with ulipristal acetate (summary of product characteristics 'not recommended')

Erythromycin

verapamil

grapefruit juice (Patients should abstain from eating large amounts of grapefruit and Seville oranges (and other products containing these fruits eg, grapefruit juice or marmalade) during the study (e.g., no more than a small glass of grapefruit juice (120 mL) or half a grapefruit or 1-2 teaspoons (15 g) of Seville orange marmalade daily)

**Potent inducers** of CYP3A4 that should not be taken with ulipristal acetate (summary of product characteristics 'not recommended')

Rifampicin, Rifabutin

Carbamazepine, Oxcarbazepine

phenytoin, fosphenytoin,

phenobarbital

primidone

St John's wort

Efavirenz, nevirapine, ritonavir

**If any of the above moderate or potent inhibitors or potent inducers of CYP3A4 are absolutely required during the study then the trial treatment (ulipristal acetate) must be discontinued.**

**P-glycoprotein (P-gP) substrates**

UA may be an inhibitor of P-gP at clinically relevant concentrations in the gastrointestinal wall during absorption. Simultaneous administration of UA and a P-gp substrate has not been studied and an interaction cannot be excluded. In vivo results show that UA (single 10 mg tablet) 1.5 hour before administration of the P-gP substrate fexofenadine (60 mg) has no clinically relevant effects on the pharmacokinetic of fexofenadine.

It is therefore recommended that co-administration of UA and P-gP substrates (e.g. digoxin and fexofenadine) should be separated in time by at least 1.5 hours.

## **Appendix 2: Data Entry into Excel Spreadsheets and Statistical Software Programmes and QC checks**

### Data Entry into Excel Spreadsheets

Data will be taken from the paper CRF. Data may be entered at the end of the study in its entirety or in batches. If data will be entered in batches, a new version of the database must be resaved and dated each time. Data entry should be performed by suitably trained and delegated staff using the 'single data entry with control checks' method.

Single Data Entry – Data is entered into the spreadsheet or database and then a visual check is performed between what is recorded on the paper source documents and what was entered into the spreadsheet or database.

The procedure is as follows:

1. Data is entered directly from the CRF into the spreadsheet ensuring all required fields are completed and in the required format e.g. correct number of decimal places.
2. Highlight all of the data that has been entered and click 'format', and ensure 'lock cell' is selected.
3. Go to review, protect sheet, and add a study specific password. This procedure will allow the data that has been entered to be locked whilst Quality Control (QC) is completed whilst still allowing further data to be added (if required) at a later date.
4. Save the excel spreadsheet using the agreed format, which identifies the file status, version and date corresponding to the data entry. This should be saved in the study specific ISF section for data management.
5. Print the spreadsheet with formulae (if applicable) unhidden. The print out must be signed and dated by the person who performed the data entry and then passed to the member of the research team who will perform the QC .
6. The data will then be QC checked as per the procedure below

